## Abstract

**Introduction:**

Antimicrobial resistance is rising, largely due to the indiscriminate use of antimicrobials. The human gut is the largest reservoir of antibiotic resistant bacteria (ARB). Individuals colonised with ARB have the potential to spread these organisms both in the community and hospital settings. Infections with ARB such as extended spectrum beta-lactamase producing enterobacteriales (ESBL-E) and carbapenemase producing enterobacteriales (CPE) are more difficult to treat and are associated with an increased morbidity and mortality. Presently, there is no effective decolonisation strategy for these ARB. Faecal microbiota transplant (FMT) has emerged as a potential strategy for decolonisation of ARB from the human gut, however there is significant uncertainty about the feasibility, effectiveness and safety of using this approach.

**Methods and analysis:**

Prospective, randomised, patient-blinded, placebo-controlled feasibility trial of FMT to eradicate gastrointestinal carriage of ARB. Eighty patients with a recent history of invasive infection secondary to ESBL-E or CPE and persistent gastrointestinal carriage will be randomised 1:1 to receive encapsulated FMT or placebo. The primary outcome measure is consent rate (as a proportion of patients who fulfil inclusion/exclusion criteria); this will be used to determine if a substantive trial is feasible. Participants will be followed up at 1 week, 1 month, 3 months and 6 months and monitored for adverse events as well as gastrointestinal carriage rates of ARB after intervention.

**Ethics and dissemination:**

Research ethics approval was obtained by London—City and East Research Ethics Committee (ref 20/LO/0117). Trial results will be published in a peer-reviewed journal and presented at international conferences.

**Trial registration number:**

ISRCTN registration number 34 467 677 and EudraCT number 2019-001618-41.

Strengths and limitations of this studyThe randomised, placebo-controlled design will control for spontaneous loss of carriage of resistant organisms.Qualitative data from participant focus groups will inform and influence a potential future trial.This study will assess feasibility; however, it is not statistically powered to assess clinically efficacy, which will need to be evaluated in a substantive trial.Mechanistic outcomes using metagenomic, metabolomic and host immune analyses could provide insight into the mechanism of action of Faecal microbiota transplant in treatment responders.The lack of investigator blinding, and the single-centre design is a limitation.

## Introduction

Antimicrobial resistance (AMR) in enterobacteriales is increasing, fuelled by the indiscriminate use of antimicrobials and inadequate infection control practices. Of greatest concern are extended spectrum beta-lactamase producing (ESBL-E) and carbapenemase producing enterobacteriales (CPE). Rates of ESBL producing bacteria carriage in our local population are 9%, with the majority being CTX-M type.^1^ Rates of detection and infections caused by ESBL-E/CRE are increasing nationally and globally,^2 3^ resulting in a significant burden of attributable death and disability adjusted life years.^4^ Antimicrobial resistant bacteria (ARB) such as ESBL-E/CPE have the capacity to spread between individuals and between organisms through horizontal gene transfer. These organisms have been responsible for several large and prolonged outbreaks worldwide.^5–7^ As well as increased morbidity and mortality, infection with resistant organisms is associated with prolonged hospital stay and increased healthcare costs.^4 8 9^ Hospitalised patients are particularly at risk of acquiring these organisms due to the treatments and procedures they receive, their comorbidities and their high exposure to antimicrobials.^5^

The microbiota of the human gut is a complex ecosystem and the largest reservoir of ARB.^10 11^ A better understanding of the human microbiome has led to a new appreciation for the role indigenous microbes play in protecting us from invading exogenous pathogens. The role of the gut microbiota in defending the host against gastrointestinal pathogens was first described in a mouse model in which streptomycin administered orally to disrupt the gut microbiota resulted in increased rate of Salmonella enterica-related infections.^12^ Antimicrobials disrupt the balance of the delicate gut ecosystem, enabling colonisation by ESBL-E/CPE and other potential pathogens. This is most strikingly evident in patients suffering from Clostridioides difficile infection (CDI), and the remarkable success of modulating this with faecal microbiota transplantation (FMT).^13 14^

Attempts to control carriage of ARB in the gut using selective digestive decolonisation are controversial, have not been widely adopted and are not recommended by expert groups.^15^ Loss of ARB colonisation has been observed in a number of patients when using FMT to treat recurrent CDI.^16^ However, these reports are nearly all case series which are uncontrolled and do not account for spontaneous loss of carriage, which can occur in up to 50% of patients following hospital discharge.^17^

The only published randomised trial of FMT to eradicate gastrointestinal carriage of ESBL-E and CPE was conducted in four academic centres in Geneva, Paris, Utrecht and Tel Aviv.^18^ Patients were randomised in a 1:1 ratio to a 5-day course of colistin and neomycin followed by FMT or no intervention. The primary outcome measure was culture of ESBL-E/CPE from stool 35–48 days following randomisation, which was achieved for 41% (9/22) of patients in the intervention arm versus 29% (5/17) in the control arm. Although the OR for decolonisation success for FMT was 1.7 (95% CI: 0.4 to 6.4), this was not statistically significant, leaving the authors to conclude that the results do not support the routine use of FMT for decolonisation. Although the study was multicentre and included a control group to account for spontaneous loss of carriage, there are several limitations with the design and conduct, making it difficult to draw firm conclusions. First, although designed as a superiority trial with a sample size calculation of 32 in each group, only 39 (61%) patients in total were randomised (due to recruitment problems). Second, patients in the intervention arm received 5 days of colistin and neomycin in addition to FMT, whereas the controls received no intervention. Thus, it is impossible to determine whether the results were due to the antibiotics (likely to have a profound effect on the gut flora) versus FMT. Third, the methods of administration of FMT varied according to recruiting site; capsules were administered in two centres (16 patients), while two used nasogastric administration (six patients). The capsules (15 administered each day over 2 days) were produced from one donation derived from 15–30 g faeces. The nasogastric preparation was derived from 40 g. There is evidence in the context of recurrent CDI that FMT preparations made with less than 50 g faeces result in poorer outcomes than those made with more than this amount.^19^ Thus, a question exists over whether the patients were under dosed, and if repeated administrations (perhaps using different donors) might be more effective. Finally, the study was not placebo controlled or blinded, although the primary outcome of stool culture at 1 month is fairly objective, there is the possibility of introducing bias in an investigator who is aware of the allocation.

Due to the limitations of the above study, the lack of other rigorously conducted, well-controlled studies and the considerable doubt that sufficient patients would be willing to participate in research of this type, we designed a feasibility study to address some of the outstanding questions.

## Methods and analysis

### Primary objectives

The primary objective of this study is to determine the feasibility and acceptability of administering encapsulated FMT to participants colonised with ESBL-E/CPE. This will be used to determine if a substantive trial is feasible.

### Primary endpoints

The primary outcome measure is consent rate (as a proportion of patients who fulfil inclusion/exclusion criteria). The success criteria for the primary endpoint are stratified. If <15% is achieved, progression to a substantive trial will not be deemed feasible. If 15%–39%, progression to a substantive trial will be deemed feasible with protocol modifications and clearly defined stop/go criteria. An overall consent rate of >40% will be taken as indicating a substantive trial is feasible.

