### Trial design

Randomised control participant-blinded, single-centre, feasibility trial with two parallel groups (FMT capsules and matched placebo). Eighty patients will be randomised 1:1 (40 will receive FMT capsules and 40 placebo) from eligible patients identified from Guy’s and St Thomas’ hospitals (figure 1 and box 1).

Box 1Participant inclusion/exclusion criteria**Inclusion criteria**To be eligible for enrolment, a participant must meet all the following criteria before undergoing any study-related procedures:Adult patients (age 18 years or older at time of consent).Current/previous patient at Guy’s and St Thomas’ NHS Foundation Trust.Ability to understand the purpose, potential benefits and risks of the study and capable of giving informed consent. The participant must be able to provide written informed consent.Documented gastrointestinal carriage of ESBL-E or CPE (stool sample) in the 21 days prior to consent.Symptomatic infection with the same target organism of interest in preceding 6 months (this needs to be microbiologically confirmed but is not restricted to any particular body site for example, could be urinary tract infection, intra-abdominal infection, blood stream infection).**Exclusion criteria**Pregnancy or planned pregnancy.Breastfeeding.Severe or life-threatening food allergy.Allergy or other contraindication to omeprazole, investigational medicinal product (IMP) or placebo ingredients.Treatment with systemic antibiotic on the day of and day prior to first IMP/placebo dosing to the end of the dosing period.Treatment with pre or probiotics in the 4 weeks prior to randomisation and for the duration of the study.Severe immunodeficiency.Systemic chemotherapy <30 days from baseline or planned chemotherapy within the upcoming 6 months.Known HIV infection with CD4 count <250 cells/uL.Known neutropenia with absolute neutrophils <1.0×10^9^.Prolonged treatment with corticosteroids (equivalent to prednisone >60 mg daily for >30 days) within 8 weeks of randomisation.Life expectancy <6 months.Swallowing disorder, oral-motor dyscoordination or likely inability/unwillingness to ingest study medication.Patients who have received another investigational drug or device within 4 months prior to randomisation.Any condition or circumstance, in the opinion of the investigator, that would compromise the safety of the patient or the quality of the study data.

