## Statistical analysis

### Sample size

As this is a feasibility study, significance tests between or within groups will not be performed for the study’s primary and secondary endpoints, therefore a power calculation has not been performed. For feasibility and pilot studies, sample sizes between 24 and 50 have been recommended to estimate a chosen parameter.^22 23^ We have chosen a 1:1 treatment to placebo ratio, therefore a total sample size of 80 would be enough to estimate the SD of the outcome in 40 treated patients, allowing for some loss to follow-up. We will also be able to estimate our expected recruitment rate of 40% (95% CI: 33 to 47) if we approach around 200 eligible patients.

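### The progression bands for consent rate give no verdict between 39% and 40%, and the expected rate of 40% falls in no band

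*Protocol article*

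**What the plan says.** The Primary endpoints section of the protocol article defines the outcome: "The primary outcome measure is consent rate (as a proportion of patients who fulfil inclusion/exclusion criteria". It then attaches a verdict to each of three ranges:

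- Low: "If <15% is achieved, progression to a substantive trial will not be deemed feasible".
- Middle: "If 15%–39%, progression to a substantive trial will be deemed feasible with protocol modifications and clearly defined stop/go criteria".
- High: "An overall consent rate of >40% will be taken as indicating a substantive trial is feasible".

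The Sample size section gives the planning value: "We will also be able to estimate our expected recruitment rate of 40% (95% CI: 33 to 47) if we approach around 200 eligible patients". The Trial design section sets the number randomised at 80, 40 per arm.

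Nothing in the article says how a rate of exactly 40%, or one between 39% and 40%, is to be classified, and it gives no rounding rule. The Secondary objectives section refers to online supplementary table 1 for the full list of progression criteria. That table is not available here.

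**The concern.** The three ranges are meant to turn the primary result into a decision about a substantive trial. The article plans no significance tests between groups, so these ranges are the decision rule for the primary endpoint. They should cover every possible result, but the middle range stops at 39% and the top range starts strictly above 40%.

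The uncovered strip is narrow, but it includes the rate the investigators expect. The verdicts on either side differ in substance. One calls for protocol modifications and defined stop/go criteria; the other does not. If the observed rate falls in the strip, somebody has to choose between them after seeing the result, which is what pre-specified criteria are meant to prevent.

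**Working it through.** **Inputs.** Bands <15%, 15%–39% and >40% (Primary endpoints). Expected rate 40%, 95% CI 33 to 47, about 200 eligible patients approached (Sample size). Planned number randomised 80 (Trial design). Exact binomial interval (Data synthesis, analysis and presentation).

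**1. The plan's own figure.** A rate of 40% in 200 patients is 0.40 × 200 = 80 consents.
- Exact (Clopper-Pearson) limits are the 2.5% quantile of Beta(80, 121) and the 97.5% quantile of Beta(81, 120): 33.2% to 47.1%.
- The Wald interval is 0.40 ± 1.96 × √(0.40 × 0.60 / 200): 33.2% to 46.8%.

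Both round to the stated 33 to 47, so the article's calculation reproduces.

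**2. Results without a verdict when n = 200.**

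| Consents | Rate | Band |
|---|---|---|
| 78 | 39.0% | feasible with modifications |
| 79 | 39.5% | none |
| 80 | 40.0% | none |
| 81 | 40.5% | feasible |

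**3. Does rounding help?** Suppose rates are rounded half-up to whole per cents before the bands are applied. Rates above 39% but below 39.5% then become 39% and enter the middle band. Rates from 39.5% to just under 40.5% become 40%, which is neither within 15%–39% nor above 40%. With n = 200 the unassigned counts are again 79 and 80.

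**4. How likely is the gap?** Let X be the number of consents, binomial with n = 200 and true rate p. The chance of no verdict is P(X = 79) + P(X = 80).

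| True rate p | P(no verdict) |
|---|---|
| 30% | 0.2% |
| 35% | 4.4% |
| 38% | 10.1% |
| 40% | 11.5% (0.0570 + 0.0575) |
| 42% | 9.3% |
| 45% | 3.8% |
| 50% | 0.2% |

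**5. What the inequality sign decides.** At p = 40%, the chance of an unqualified feasible verdict is P(X ≥ 81) = 46.9% under the rule as written and P(X ≥ 80) = 52.7% if 40% is included. The difference is P(X = 80) = 5.8%.

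**6. Stopping at a fixed number of consents.** Suppose recruitment ends at 80 consents and the number approached varies. The rate is 80/200 = 40.0% and 80/205 = 39.02%, so every denominator from 200 to 205 lands in the gap. With 199 the rate is 40.2% (top band) and with 206 it is 38.8% (middle band).

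**The case against.** The strongest reply is that little turns on the gap. It lies between two verdicts that both allow progression. Nothing is missing at the stop boundary: below 15% is not feasible, and 15% upward is. A reader might infer that the primary decision rule as a whole is undefined, or that a result in the gap could turn progression into non-progression. The text does not support that. No rate in the gap is near the stop boundary, and no estimate, interval or safety conclusion changes.

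A reader might also infer that the planned result itself, 80 out of 200, has no verdict. The article prints no such fraction. It says about 200, and the 80 is the number randomised, not the number consenting. The Consent section places consent before eligibility screening, so consents may exceed 80. The point does not need the fraction, because the expected rate of 40% is stated outright.

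It is also fair to say that whole-per-cent limits are common shorthand, and that the strict sign was probably a slip for 40% or more. That explains the wording, but a rounded 40% is still left without a band.

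Finally, supplementary table 1 may word the limits correctly, and the analysis plan promised before database lock could set a rounding convention. That limits what can be said about the trial as a whole. It does not make the Primary endpoints text right, since that section states these bands as the success criteria without qualification.

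**Conclusion.** The bands are wrong as written, and the error is minor to moderate. They are not exhaustive: a consent rate above 39%, up to and including 40%, has no verdict, and the expected rate of 40% is unassigned with or without rounding to whole per cents. What is left open is only whether the trial progresses as feasible or under "progression to a substantive trial will be deemed feasible with protocol modifications and clearly defined stop/go criteria".

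The 11.5% chance of landing in the gap is close to the worst case, because it takes the true rate to be the expected 40%. It falls to about 4% at 35% or 45% and is negligible at 30% or 50%. The Introduction itself voices considerable doubt about patients' willingness to take part, so 40% is not assured. These figures assume exactly 200 eligible patients approached and independent decisions to consent. The gap in the bands depends on neither assumption.

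**What to change.** Before the consent rate is known, restate the bands so that they meet and apply to the unrounded proportion. One example is below 15%, not feasible; 15% or more but below 40%, feasible with modifications and stop/go criteria; 40% or more, feasible. Placing 40% in the top band looks like the intent, but the text does not settle it, so the sponsor should confirm. Check supplementary table 1 and carry the same cut-points into it and into the analysis plan.

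The exact 95% interval is already planned for the proportion accepting randomisation, so no new analysis is needed. The cost is one sentence. Design, sample size and data collection are unaffected.

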### Secondary objectives

The secondary objectives are to assess other feasibility aspects of conducting a substantive trial, to evaluate the safety and tolerability of FMT in this patient population and to provide early evidence of efficacy. These measures should inform a future trial, such as determining the primary (efficacy) outcome and sample size, if progression criteria are met. A full list of criteria for progression to a substantive trial is detailed in online supplementary table 1.

10.1136/bmjopen-2020-038847.supp1Supplementary data

### Secondary feasibility endpoints

Proportion of patients fulfilling inclusion/exclusion criteria.Proportion of patients receiving FMT/placebo (as a % of those consenting).Proportion of patients returning for follow-up visits (face-to-face visit at day 40).Proportion of patients providing follow-up stool samples (days 10, 40, 100 and 190).Ability to recruit sufficient healthy donors to manufacture all FMT doses to meet demands of this and a future substantive randomised controlled trial (RCT). Assessed by delay in dosing patients (measured in days).

### Additional feasibility assessments will include the following:

Collection of data that may be used in estimating of costs/resources needed to provide FMT in the National Health Service (NHS).An embedded qualitative study to explore views and experiences of research participants.

### Secondary efficacy endpoints

Gastrointestinal carriage of CRE/ESBL-E (detected/not detected) by stool culture over time (days 10, 40, 100 and 190).Gastrointestinal carriage of CRE/ESBL-E (detected/not detected) by multiplex PCR over time (days 10, 40, 100 and 190).

### Secondary safety and tolerability endpoints

Proportion of patients experiencing reflux following administration of FMT.Proportion of patients suffering intolerable (resulting in withdrawal from the study) gastrointestinal side effects (including diarrhoea, constipation, abdominal pain, flatulence and bloating). This will be assessed by direct questioning and completion of a short patient questionnaire.Identification of unanticipated harms involved with administration of FMT.Occurrence of any adverse event/serious adverse event.

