### Consent

Informed consent (for both healthy donors and patient-recipients) will be obtained prior to any trial related activities, including screening for eligibility. Potential participants will be given the participant information sheet and allowed enough time to read thoroughly and discuss with others outside the study team (eg, family, friends and general practitioner) (see online supplementary table 2). Participants are free to withdraw from the trial at any time without giving reasons. Data and samples collected up to the point of withdrawal will only be used after withdrawal if the participant consented for this. Patients who lack capacity will not be enrolled in this study. Where a participant consents but later becomes incapacitated, the original consent given endures the loss of capacity, providing that the trial has not significantly altered.

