### Study intervention

FMT for this trial will be prepared in a lyophilised, encapsulated form in accordance with Good Manufacturing Practice principles and under manufacturing authorisation for an IMP from the Medicines and Healthcare Products Regulatory Agency. Our centre has recently provided FMT for a Clinical Trial of an Investigaional Medicinal Product (CTIMP) for cirrhosis and this follows similar processes.^20^ Healthy donor inclusion and exclusion criteria and screening and eligibility questionnaire are described in online supplementary table 3 and 4.

The product contains 0.9% sodium chloride and 5% trehalose (cryoprotectant) as excipients. A minimum of 80 g faeces from each donor will be used to manufacture one batch of five capsules. Following lyophilisation, the material will be encapsulated in five size 0 delayed release methylcellulose capsules (DRcaps, Capsugel, Livingston, UK). Placebo capsules will contain microcrystalline cellulose. The capsules for the FMT and placebo will be identical in appearance. The capsules are coloured Swedish orange, resulting in an opaque appearance through which the contents cannot be seen.

FMT donors are carefully screened healthy volunteers with a body mass index between 18 and 30. Donors undergo questionnaire screening for risk factors and testing for a range of infectious agents as previously described and in accordance with national guidelines (see appendix A for full details).^21^ FMT material is traceable from donor to recipient. Aliquots of donor stool will be kept for 30 years to allow for future testing if required.

At baseline, participants will have their medication history recorded, including over the counter preparations and supplements as well as pre/probiotics. Vital signs, height and weight and baseline blood biochemistry and haematology will be collected. Additionally, a serum sample will be stored to allow future testing in the event of a possible transmission event. If female and of childbearing age, a urinary pregnancy test will be performed. An EQ-5D questionnaire will also be administered.

Encapsulated FMT (IMP) and placebo will be dispensed by study staff to trial participants over 3 consecutive days (or over 5 days if over a weekend). Patients will be fasted for 4 hours and be pretreated with omeprazole on the morning on the FMT (40 mg on first dosing day and 20 mg on the 2 subsequent dosing days).

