### Evaluations during and after treatment

Follow-up events will be scheduled for all participants at 1 week, 1 month, 3 months and 6 months after end of therapy. If an outpatient, the visits at 1 week, 3 months and 6 months will be conducted by telephone, with the participant returning a stool sample by post. The follow-up at 1 month will be face to face and will include a blood sample for immune analyses. All visits will involve completion of an EQ-5D questionnaire (see figure 2 for additional details).

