### Qualitative study

A qualitative study of participant’s experiences will be undertaken and comprises a focus group interview with a minimum of eight participants. Ideally, the group will include at least two patients who were approached but did not agree to participate. The aim of these discussions is to identify facilitators and barriers to delivering the trial, and whether there are any aspects of the trial that should be changed. The interviews will be semistructured and recorded to aid writing up the study report. Objectives of the focus group will include identifying ways of increasing recruitment and retention; identifying ways of broadening participation in the trial to improve diversity of population; improving understanding of how participants join trials and experience of participation; measuring reasons for non-adherence to the trial medication; exploring stakeholders’ views of acceptability of the trial design; strengthening the ethical conduct of the trial, for example, informed consent procedures; addressing any local issues which may impact on the feasibility of a substantive trial.

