### Data synthesis, analysis and presentation

A statistical analysis plan will be written by the trial statistician and signed off prior to database lock. The study will be reported in accordance with the Consolidated Standards of Reporting Trials extension for pilot and feasibility studies.

The proportion of patients who accept the offer of randomisation will be reported with 95% CIs computed by the exact binomial method. No statistical tests for significant differences between treatment groups will be performed. In addition to summary statistics of the secondary outcomes, all harms and withdrawals will be reported with 95% CIs. Patients will be analysed in the groups to which they are randomised in accordance with intent to treat principals.

The protocol has been designed to place minimal burden on patients and case report forms are only capturing essential data. It is inevitable that there may be some missing data, which will be reported by treatment group with reasons for missingness described, where possible. Since this is a feasibility study, we do not plan to impute missing data.

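### The "intolerable" gastrointestinal side effects endpoint counts only patients who leave the study, so it misses those who stop the capsules but stay in follow-up

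*Protocol article*

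**What the plan says.** Under Secondary safety and tolerability endpoints, the protocol article defines the endpoint as the "Proportion of patients suffering intolerable (resulting in withdrawal from the study) gastrointestinal side effects", with diarrhoea, constipation, abdominal pain, flatulence and bloating among the effects named. On measurement it says: "This will be assessed by direct questioning and completion of a short patient questionnaire".

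Under Study intervention, capsules are "dispensed by study staff to trial participants over 3 consecutive days (or over 5 days if over a weekend". Under Evaluations during and after treatment, the article sets out the later contacts: "Follow-up events will be scheduled for all participants at 1 week, 1 month, 3 months and 6 months after end of therapy". For outpatients, three of these four contacts are by telephone with a posted stool sample.

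The Consent section uses withdrawal to mean leaving the trial: "Participants are free to withdraw from the trial at any time without giving reasons". The analysis section states: "Patients will be analysed in the groups to which they are randomised in accordance with intent to treat principals".

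**The concern.** Stopping a short course of capsules and leaving a 6-month study are different events. A patient who declines the second or third day's capsules because of diarrhoea or abdominal pain has little reason to give up a light follow-up schedule, and an intention-to-treat analysis needs that patient retained. The definition records only the second event.

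The endpoint therefore depends partly on willingness to remain in follow-up: the better the retention, the lower the apparent intolerance. Safety and tolerability are named among the secondary objectives, and the article says that these measures should inform a future trial. Anyone planning that trial would want to know how many patients could not finish the multi-day course because of its side effects.

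**Working it through.** **Step 1. What the definition includes.** Consider four kinds of patient with gastrointestinal side effects:

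| Patient | Counted as written? | Counted if missed or stopped doses also qualify? |
|---|---|---|
| Completes capsules, stays in study | No | No |
| Misses or stops capsules, stays in study | **No** | **Yes** |
| Misses or stops capsules, leaves study because of the effects | Yes | Yes |
| Completes capsules, later leaves study because of the effects | Yes | Yes |

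Only the second row differs. The patients counted as written are a subset of those counted under the wider definition, so in each arm the written endpoint is equal or lower. This fixes the direction for each arm's proportion. It does not fix the direction for the difference between arms, because placebo patients may also stop and stay.

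**Step 2. Can the second row occur?** Yes. There are three dosing days, so a course can be left incomplete. Follow-up is scheduled for all participants, and nothing in the article makes stopping the capsules a reason to leave the study.

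**Step 3. Does another listed endpoint count this patient?**

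- Proportion receiving FMT or placebo (Secondary feasibility endpoints): specifies neither completion of all doses nor the reason for stopping.
- Any adverse or serious adverse event: should record the symptom but, as described, not that it ended treatment.
- Harms and withdrawals with 95% CIs (Data synthesis, analysis and presentation): does not list discontinuation of study product.
- Qualitative study: "measuring reasons for non-adherence to the trial medication" is an objective of the focus group, not an endpoint measured in all participants.

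None identifies discontinuation because of gastrointestinal effects.

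**Step 4. Size.** The article gives no figure for this endpoint, so there is none to reproduce. Inputs:

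- n = 40 per arm (Trial design), all taken as the denominator.
- W = 1 patient who leaves the study because of gastrointestinal effects (assumed).
- S = 0 to 4 patients who miss or stop capsules for such effects but stay (assumed).

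Reported as written: W/n = 1/40 = 2.5%, exact (Clopper-Pearson) 95% CI 0.1% to 13.2%, whatever S is. Counted with stoppers: (W + S)/n. Shortfall: S/n, that is 1/40 = 2.5 percentage points per patient.

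| S | Reported | Counted with stoppers | Exact 95% CI of the latter |
|---|---|---|---|
| 0 | 1/40 = 2.5% | 1/40 = 2.5% | 0.1% to 13.2% |
| 1 | 2.5% | 2/40 = 5.0% | 0.6% to 16.9% |
| 2 | 2.5% | 3/40 = 7.5% | 1.6% to 20.4% |
| 3 | 2.5% | 4/40 = 10.0% | 2.8% to 23.7% |
| 4 | 2.5% | 5/40 = 12.5% | 4.2% to 26.8% |

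**The case against.** The strongest reply is that the article states its threshold openly, so a reader knows what the number means, and that the missed patient's symptoms are not hidden. Gastrointestinal effects are sought by questioning and questionnaire, any adverse event is an endpoint, and harms are reported with confidence intervals. This stands in part. A reader might infer that such a patient is recorded as having tolerated the capsules, or that the trial's whole account of tolerability is too favourable. The article supports neither inference: one endpoint among several is affected. What the other endpoints do not supply is the link between the symptom and the end of treatment.

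A second reply is that the article is condensed, and that the full protocol or case report form may separate stopping product from leaving the study. That may be so. The point, however, concerns a definition that the article does state, and it would apply even if the form recorded both events.

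Third, the opportunity is limited. Dosing is brief, staff dispense the capsules, most patients are expected to be inpatients, and only effects that arise before the last dose can cause a dose to be missed. This stands, and it is a reason to expect few such patients. It does not change the direction of the error.

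A reader might also infer that events in patients who withdraw are lost, because the Consent section says: "Data and samples collected up to the point of withdrawal will only be used after withdrawal if the participant consented for this". The documents do not support that. The sentence permits use with consent, that permission may be sought at enrolment, the consent form is not shown, and withdrawals themselves are to be reported.

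**Conclusion.** The concern holds for this one endpoint. As worded, it omits patients whose gastrointestinal side effects ended or interrupted treatment but who stayed in the study, and it can only understate intolerance within an arm. Each such patient costs 2.5 percentage points in an arm of 40. Under the assumed counts the shortfall runs from 0 to 10 points (12.5% − 2.5%). The true size is unknown, because the article gives no discontinuation rate, and it is zero if nobody stops and stays.

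A reader might infer that a decision to proceed turns on this number. The article does not show that. The only progression thresholds it prints concern the consent rate, and the full list of criteria is in a supplementary table that is not at hand. The primary outcome is unaffected. This is a modest, inexpensive correction to a secondary endpoint.

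**What to change.** Define the endpoint as the proportion of patients, by arm, with gastrointestinal side effects that led to a missed or stopped study dose or to withdrawal from the study. Report discontinuation of study product and withdrawal from the study as two separate events, so that the strict figure now planned can still be read off. This changes only measurement and reporting and sets no dose or stopping rule.

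The costs are a change of endpoint wording and a record of the reason for each missed dose, if the case report form does not already hold one. The reported intolerance rate may rise. Effects that begin after the last dose will still count only if they lead to withdrawal from the study, and otherwise remain in the adverse event summary.
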